## Abstract

**Background:**

In 2020, New Mexico had the highest alcohol related death and the 11th highest drug overdose rate in the U.S. Towards the long-term goal of addressing this public health problem, we are implementing and evaluating an multi-level intervention designed to identify adults at risk of substance use disorder (SUD) and encourage linkage to and retention in treatment. The first level includes equipping the ED and medical inpatient units of a safety-net hospital with a method to screen individuals at risk of a SUD. The second level includes Seeking Safety (SS), a trauma-specific treatment for PTSD and SUD; and pharmacotherapy for SUD. Motivational Interviewing (MI) is used throughout both levels. Using the SPIRIT guidelines and checklist, this study protocol describes the multi-level intervention and the methodology we are using to assess feasibility and effectiveness.

**Methods:**

We are using a Type 1 hybrid implementation design with a non-randomized approach (ISRCTN registration # ISRCTN33100750). We aim to enroll 110 adults (
≧18
) who screen positive for unhealthy use of alcohol, prescription medications (used nonmedically) and/or illicit drugs. Peer support workers are responsible for screening, using MI to increase engagement in screening and treatment and delivery of SS. Pharmacotherapy is provided by addiction clinical specialists. Treatment is provided post hospital discharge via telehealth to increase access to care. Participants are identified through (1) review of electronic health records for individuals with a chief or secondary complaint or mental health condition relating to alcohol and/or other drug use, (2) referrals from clinical staff and (3) screening in the ED and medical inpatient units. Feasibility is being measured through process data. Effectiveness will be determined by changes in two primary outcomes: (i) PTSD symptom severity; and (ii) substance use.

**Discussion:**

Our study will expand on research related to the implementation of treatment strategies for patients presenting at EDs and admitted to medical inpatients units wherein there is a significant window of opportunity to link patients with follow-up behavioral and clinical services for alcohol and/or drug misuse. The challenges associated with implementation and strategies that have been helpful to address these challenges will further inform the field.

## Background

In 2020, New Mexico (NM) had the highest alcohol related death rate in the U.S.; 86.6 deaths per 100,000 compared to 41.5 nationally (1). It also had the 11th highest drug overdose rate in the U.S., with 801 total deaths due to drug overdose (2). Recent data indicate an even worsening trend, with drug overdose rates increasing in NM at a far greater rate compared to the rest of the U.S. The drug overdose death rate in NM increased from 26.3 per 100,000 in 2011 to 51.6 per 100,000 in 2021. In contrast, the drug overdose death rate in the U.S. was 13.2 per 100,000 in 2011 and 32.4 per 100,000 in 2021 (2). Noteworthy, is that “approximately 75% of drug overdose deaths in 2021 involved at least one opioid and 66% of deaths involved synthetic opioids (e.g., illicitly manufactured fentanyls)” (3)Among the U.S., NM has the third highest percentage of Native Americans (12%) (4) and consistent with national level data, Native Americans in NM have a much higher risk of alcohol poisoning deaths than any other race group (5).

The consequences of excessive substance use have been far reaching for New Mexicans, including high rates of domestic violence, fatal crashes involving intoxicated drivers and deaths due to alcoholic liver disease, cirrhosis, unintentional injuries and suicide (6). Our ability to improve this public health problem is based on the availability of evidence-based care, as well as the success to which those with substance use disorders (SUD) are identified clinically, are referred to treatment, can access treatment and initiate treatment.

Individuals with a SUD often present to the emergency department (ED) or are admitted to an inpatient unit of a hospital for a variety of reasons, including substance use related injuries, infections and overdoses (7). Nearly half of all ED visits in the US are categorized as being related to SUDs (8) and substance abuse related admissions to intensive care or other hospital medical units are widespread (9). As a result, hospital-based settings provide an opportunity to actively engage patients in a discussion about the need for treatment and link them into appropriate services and support (8).

Unfortunately, many EDs and inpatient units struggle with not having enough staff or staff with expertise or experience to effectively engage with individuals with SUDs, including telling them about their treatment options and linking them to care in a non-rushed and non-judgmental way in times of crisis (10–15). To address this need, programs have been placing peer support workers (PSWs) within EDs to support people with SUD (16). PSWs are “people who have been successful in the recovery process who help others experiencing similar situations” (17). Other terms for this workforce include peer recovery support services, peer recovery coach/specialist and peer navigator/advocate.

Provision of peer support services is an evidence-based practice for SUD care and evidence for the benefits of these services is accruing (13, 18–21). When placed in the ED, PSWs have been associated with greater SUD treatment engagement, especially with high-risk populations, and shorter days to initiation for substance use treatment (13, 15, 18, 22–24). However, there is scant data on the feasibility of employing PSWs in the ED and medical inpatient units who can support screening and linkage to care provided via telehealth. Furthermore, the studies conducted thus far have focused on PSW interventions that have been implemented in EDs that serve mostly urban populations. Research on the effectiveness of these interventions within hospitals that serve rural and tribal populations is needed, given the high rates of SUD in these communities and the increasing use of EDs among individuals with SUD, especially from rural areas (25).

To the extent possible, an unencumbered transition of care from the hospital to outpatient treatment is critical for individuals with SUD who want to engage in treatment for their SUD before being discharged. This includes making access to treatment as easy as possible, especially for groups more likely to face barriers to accessing care. Telehealth has been shown to increase access to addiction treatment, particularly in rural areas where services within communities are limited and transportation to services outside of the community is unavailable or difficult (26, 27). Telehealth for SUD treatment has also been shown to be associated with increased retention in SUD treatment and increased therapeutic alliance (28).

To increase the likelihood that (1) those at risk of a SUD who present to the ED or are admitted to an inpatient unit are identified and referred to treatment, and (2) those determined eligible are referred to and can access treatment, we are conducting a multi-level implementation study assessing the feasibility and effectiveness of a combination intervention strategy comprised of several evidence-based and practical interventions (29).

The objective of our study is to evaluate the feasibility and effectiveness of an integratedmulti-level intervention that identifies individuals at risk of a SUD and encourages linkage to and retention in community-based SUD treatment. Using the SPIRIT guidelines and checklist (http://www.spirit-statement.org/), this study protocol describes the multi-level intervention and the methodology we are using to assess feasibility and effectiveness.

## Methods: participants, multi-level intervention, and outcomes

### Study design

This study uses a Type 1 hybrid implementation design with a non-randomized approach (30) (see **Figure 1**). While the primary focus of our study is to test the intervention, we are also very interested in understanding implementation related factors. As a result, we are collecting process data along every step of **Figure 1**, including for example, the number of referrals and patients screened, number of patients determined eligible and reasons for ineligibility, number of patients who agree to treatment and attend at least one appointment.

**Figure 1 f1:**
[figure not shown]
Overview of Participant Flow Through the Multi-Level Intervention and Study Enrollment*. *Footnote: The first level of the multi-level intervention includes equipping the ED and medical inpatient units of a safety-net hospital with a method to screen individuals at risk of a SUD. The second level includes Seeking Safety (SS), a trauma-specific treatment for PTSD and SUD; and pharmacotherapy for SUD. Motivational Interviewing (MI) is used throughout both levels.

### Study site

The study site is a safety-net hospital located in Sandoval County, NM. Sandoval County is the 4^th^ most populous county in NM, with 131,561 residents and covering 3,716 square miles. 40% of the residents are Hispanic and 14.1% are Native American (NA). Most health care services in Sandoval County are available in the “metro” corner, which is only 150 square miles and where two-thirds of the county’s population reside. The “nonmetro” area is home to 13 sovereign tribal nations, including 10 Pueblos, two Navajo chapter houses and a portion of the Jicarilla Apache reservation. This is the second highest number of reservations of any county in the U.S. The nonmetro area covers over 3,500 square miles and residents struggle with limited access to healthcare and high rates of poverty, mental health problems, substance use and suicide. In Sandoval County, the alcohol related death rate for NA is 174.2 per 100,000 compared to 56.0 and 35.1 per 100,000 for the overall state and U.S., respectively (31). Sandoval County is one of the top five counties with the highest number of methamphetamine-involved overdose deaths and has the 2nd highest number of opioid overdose related ED visits in the state (N=363, 6.1%) (31). The study period is October 2022 – September 2024. This study has been registered on the ISRCTN registry # ISRCTN33100750.

The study site hospital houses 72 inpatient beds, divided between two medical surgical units and one intensive care unit. The ED has 20 licensed beds. Fiscal year 2021 data from the study site hospital showed that 1,366 patients, representing 1,958 visits, accessed the ED with a SUD diagnosis (including alcohol use disorder). 75% of all inpatient discharges from the medical units with a behavioral health diagnosis had a SUD. Compared to 2020, the number of individuals with a primary diagnosis of SUD increased by 75% in the ED and 48% in the medical inpatient units in 2021. For the past three years, Native Americans comprised 56% of all admissions to the ED for alcohol use disorder. Furthermore, 30% of the ED behavioral health visits in 2021 were from designated rural communities of Sandoval County.

### Eligibility criteria

Participants are adults 18 years of age or older who present to the ED or are admitted to a medical inpatient unit and who have screened positive for unhealthy use of alcohol, prescription medications (used nonmedically) and/or illicit drugs on the National Institute on Drug Abuse Tobacco, Alcohol, Prescription medication and other Substance Use (TAPS) (32). Individuals with unhealthy tobacco use only are excluded from the target population. Participants are excluded from the program if they are under 18 years of age, cannot speak English, are cognitively-impaired and therefore unable to provide consent, or do not wish to participate in treatment. Based on previous research with this population, the percent of non-English speaking individuals in our target population is less than one percent. Individuals who are not included in the study are still eligible to receive services through SRMC TH-SUD treatment and any other services at SRMC. The PSWs are responsible for conducting the screening and determining eligibility.

### Multi-level intervention

Our multi-level intervention combines several evidence-based and practical interventions (see **Figure 1**). The first level includes equipping the ED and medical inpatient units of a safety-net hospital with a method to screen individuals at risk of a SUD. The second level includes Seeking Safety (SS), a trauma-specific treatment for PTSD and SUD; and pharmacotherapy for SUD. Motivational Interviewing (MI) is used throughout both levels. Each of these interventions will be described in more detail below. SS and pharmacotherapy for SUD is provided post discharge via telehealth to increase access to care.

### Hiring and training PSWs

PSWs are key to the implementation of our intervention. PSWs are hired through the study site hospital human resource office. Job postings were developed specifically for PSWs positions for this study. Both full-time and part-time employment opportunities are available for PSWs. Applicants that reflect the race/ethnicity of the target population are given priority as well as individuals in recovery from substance use disorders. All PSWs receive initial and ongoing training for both MI and SS. The MI training consists of two half-days; Part One covers the SPIRIT of Motivational Interviewing, the importance of accurate empathy, understanding ambivalence and resistance, and basic skills: OARS (open ended questions, affirmations, reflections, summary). Part Two reviews SPIRIT, OARS and ambivalence and teaches the basic MI skill of CHANGE Talk using DARN CATS, skillful responses and double-sided reflections. The SS initial training consists of two half-days covering an introduction to the intervention as well as its implementation. Ongoing training is provided for PSWs in both MI and SS to increase fidelity to the models. Ongoing MI training is provided through monthly learning communities which cover topics such as recognizing the stages of change and simple and complex reflections. Ongoing SS training is provided through weekly practice sessions (including role playing) between the clinical supervisor and PSWs. PSWs also complete a number of other trainings to prepare them for working in a rural hospital environment and with the target population, such as Cultural Sensitivity, Clinical Documentation, Suicidal Ideation Response for Telehealth, pharmacotherapy for SUD, and TAPS administration. Finally, PSWs meet with a dedicated clinical supervisor once per week to discuss any difficulties with patients or questions about clinical processes.

### Screening for SUD in the hospital

The identification of individuals at risk of SUD in the ED and medical inpatient units is a major component of the intervention. PSWs use the TAPS screening tool to determine study eligibility. The TAPS includes two parts: firstly, five questions that ask about substance use (i.e., tobacco, alcohol, non-medical use of prescription drugs, and illicit drugs) in the past 12 months, and secondarily among those who screen positive on part 1, nine questions about substance use in the past three months (32).

There are multiple ways in which individuals are identified to complete the TAPS. The first way is with a brief screening tool that is completed on individuals 18 years of age or older who present to the ED. The brief screening tool includes two questions: (1) how many times in the past year have you had 4 or more drinks in one day, and (2) how many times in the past year have you used a recreational drug or used a prescription medication for non-medical reasons? Recreational drugs include methamphetamines (speed, crystal) cannabis (marijuana, pot), inhalants (paint thinner, aerosol, glue), tranquilizers (benzodiazepines), barbiturates, cocaine, ecstasy, hallucinogens (LSD, mushrooms) or opioids (fentanyl, heroin). Individuals whose response is >1 on the brief screen are invited to complete the TAPS. The second way PSWs identify individuals to complete the TAPS is through targeted identification of ED patients and inpatients with a chief or secondary complaint or mental health condition relating to alcohol and/or other drug use. To do this, PSWs review the electronic health records of ED patients and inpatients for whom substance use was a presenting complaint. PSWs also attend ED rounding, huddles (that occur during shift changes where the PSWs meet with the incoming ED providers) and obtain referrals from clinical staff through TigerConnect, which is a secure real-time messaging app used by hospital staff.

### Communication post screening

PSWs are responsible for informing those determined at risk of SUD about the results of the TAPS screen and about the specifics of the community-based intervention, including the treatment options, the method of delivery (telehealth) and that because the intervention is grant funded the treatment that they are being offered is free. When sharing the results of the TAPS screen and the reason for moving on from the first part of the TAPS to the second part, PSWs are required to follow a script to ensure consistency among the team. PSWs provide patients a treatment menu that briefly describes both interventions, SS and pharmacotherapy, with words and pictures. Patients are asked to choose which services they would like to participate in; SS only, pharmacotherapy only or both. PSWs also provide patients with a “discharge packet” that includes instructions on how to access telehealth, hard copies of the SS materials, and a discharge summary which lists the services they agreed to participate in as well as contact information for the PSW they met with.

Assessing Barriers to Online Treatment. Because both SS and pharmacotherapy for SUD is provided via telehealth, PSWs are responsible for checking with patients about their access to treatment online. PSWs can provide patients who do not have a way to access treatment a cell phone with monthly paid service.

### Motivational interviewing

PSWs use Motivational Interviewing (MI) to encourage patients to complete the brief screen and the TAPs. They also use MI to engage those determined eligible into treatment. MI is a brief intervention that helps individuals resolve ambivalence about behavior change by eliciting and enhancing intrinsic motivation for change (33). A large body of research supports the effectiveness of MI for substance use (34).

### Seeking safety

SS is an evidence-based, present-focused, manualized brief treatment that uses cognitive-behavioral approaches designed to target trauma, PTSD and SUDs (35). SS provides coping skills that enable participants to cope in safe ways without substances and without harmful behaviors. The literature on the effectiveness of SS is vast and includes evidence on the effective delivery of SS by PSWs (36). Studies have shown positive outcomes including decreases in substance use, PTSD and trauma related symptoms, and improvements in social adjustment, suicidal thoughts, coping, sense of meaning and quality of life (37–39). SS includes 25 topics that cover behavioral, interpersonal and cognitive domains. However, because SS is designed for a high level of flexibility and topic order can vary, similar to other studies of SS, we selected 10 modules most relevant to our target population to begin with (36). The modules include: (1) Safety, (2) PTSD: Taking Back Your Power, (3) When Substances Control You, (4) Detaching from Emotional Pain, (5) Asking for Help, (6) Coping with Triggers, (7) Discovery, (8) Setting Boundaries in Relationships, (9) Recovery Thinking, (10) Honesty. With up to 97.4% of individuals with SUD having a history of trauma, a trauma-specific focused intervention can be a critical component of SUD treatment (40). PSWs are responsible for delivering SS one-on-one with patients via telehealth. Appointments are scheduled by PSWs or a Patient Assistant Representative. SS materials are either sent to the patients electronically or mailed depending on preference.

### Pharmacotherapy for SUD

Pharmacotherapy for SUD involves the use of FDA approved medications that are often combined with counseling and behavioral therapies for people diagnosed with SUD. Pharmacotherapy for SUD has proven to be clinically effective with respect to reducing substance use, cravings, withdrawal symptoms and preventing overdoses (41, 42). Evidence also suggests that combining counseling services, including MI, with pharmacotherapy for SUD, improves treatment retention (43). FDA approved drugs for opioid use disorder include methadone, buprenorphine, and naltrexone. While pharmacotherapy for SUD is mostly known for opioid use disorder, because of the large prevalence of alcohol use disorder among the target population, our addiction specialists are also offering approved FDA medications for AUD, including acamprosate, disulfiram, and naltrexone. For short term withdrawal, prescriptions include gabapentin and carbamazepine.

### Outcomes

**Table 1** provides an overview of our primary, secondary and other outcomes, including the specific tool used to measure the outcome and measurement time point.

**Table 1 T1:** Overview of data collection.

Domain	Data Collection Tool	Time Point	Variable Type
Post-Traumatic Stress Disorder Symptom Severity	PTSD CheckList – Civilian Version (PCL-C) (44)	Baseline and every 60 days	Primary Outcome
Substance Use	Addiction Severity Index (45)	Baseline and every 60 days	Primary Outcome
Demographics	Age, race, ethnicity, gender (assigned at birth and current identity), relationship status, level of education, income level, employment status, health insurance status and provider, housing status	Baseline evaluation	Covariates
Criminal Activity Involvement	Criminal Justice Questionnaire (developed by first and second author)	Baseline and every 60 days	Secondary Outcome and Predictor
Motivation to Change	The Change Questionnaire (46)	Baseline and every 60 days	Secondary Outcome and Predictor
Treatment Satisfaction	Client Satisfaction Questionnaire (CSQ-8) (47)	Baseline and every 60 days	Secondary Outcome and Predictor
Quality of Life	36-Item Short Form Survey Instrument (SF-36) (48)	Baseline and every 60 days	Secondary Outcome and Covariate
Past Barriers to Substance Use Treatment	Barriers Questionnaire (49)	Baseline and every 60 days	Secondary Outcome and Covariate
Perception of Recovery	The Questionnaire about the Process of Recovery (QPR) (50)	Baseline and every 60 days	Secondary Outcome and Covariate
Self-Stigma	Substance Abuse Self-Stigma Scale (51)	Baseline and every 60 days	Secondary Outcome and Covariate
Substance Craving	3-Item Substance Craving Scale (52)	Baseline and every 60 days	Secondary Outcome and Covariate
Emergency Department Utilization	Services Use Questionnaire and EHR (developed by first and second author)	Baseline and every 60 days	Secondary Outcome and Covariate
Hospital and/or treatment facility utilization	Services Use Questionnaire and EHR (developed by first and second author)	Baseline and every 60 days	Secondary Outcome and Covariate

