### Surveys completed by hospital staff and PSWs

To further our understanding of feasibility, we are also collecting data from hospital personnel on perceived acceptability, appropriateness, and feasibility of the screening component of our intervention. Acceptability refers to how those targeted and involved in implementing the program react to the screening. Appropriateness refers to the extent to which the screening fits within the ED and medical inpatient settings. Feasibility refers to the extent to which the screening can be successfully implemented within the ED and medical inpatient settings. These constructs will be measured by three established self-report measures: the (i) Acceptability of Intervention Measure (AIM), (ii) Intervention Appropriateness Measure (IAM), and (iii) Feasibility of Intervention Measure (FIM). The AIM, IAM and FIM include 4 items rated on a 5-point Likert scale ranging from “completely disagree” to “completely agree” (53). Higher scores indicate higher perceptions of acceptability, appropriateness, and feasibility. The measures take approximately one minute each to complete. They will be completed online by PSWs on the study team and all providers within the ED and inpatient settings, including nurses, emergency physicians, inpatient physicians and other clinical support staff. Since these instruments were not designed to be completed by those who receive the intervention, we intentionally included the Client Satisfaction Questionnaire-8 [75} as part of the battery of measures (see **Table 1**) to provide an opportunity for participants enrolled in the study to voice their opinions about the acceptability of the intervention.

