### Participant interviews and consent

Once an individual agrees to engage in treatment, the PSW provides details about the opportunity to participate in a prospective follow-up cohort study. Individuals who are interested in participating sign a release of information agreeing to be contacted by a member of the research team. A member of the research team is then responsible for contacting individuals to provide further information about the study, obtaining consent for those who agree to participate and conducting baseline and follow-up interviews. Follow-up interviews are being conducted every 60-days post baseline. The consent process and all data collection is conducted by phone or a HIPAA compliant video conferencing platform. Individuals are compensated for their participation in the study with a $60 merchandise gift card for completing the baseline interview and $90 for every follow up assessment. The research team makes multiple attempts at varied times of the day and day of the week to consent individuals and complete baseline and follow up interviews. Participants are contacted via phone, text, mail and email. Participants are also offered a phone with monthly cell phone service to increase the likelihood of their participation in the study. Interviews range between 45 and 60 minutes. **Table 1** provides an overview of all data being collected during participant interviews, including the data collection tools and time point.

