#### Effectiveness of the multi-level intervention

Two primary outcomes will inform our assessment of effectiveness: change in PTSD symptom severity [as measured by the Post-Traumatic Symptom Checklist (44)] and change in substance use [as measured by the Addiction Severity Index (45)]. We will use a pre-post intervention multilevel regression model analysis to examine the change in our primary outcomes of interest. The goal of the multilevel models will be to look for significant and meaningful change in the pre-post scores of our primary outcomes, PTSD symptom severity and substance use, based on the impact of the client’s predictor variables; criminal justice involvement, motivation to change and client treatment satisfaction (see **Table 1**).

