To assess the impact of our covariates and secondary outcomes of interest, we will apply a multi-step approach to examine the significance of our independent variables. First, we will test for significant pre-post differences in our secondary outcomes to assess the impact of the variables from the start to finish of the client’s time in the program using parametric paired t-tests. Results of the paired tests will provide results to the significance of the impact pre-post on the client’s perceptions of the program and will provide validation of using the markers as covariates in the regression model. Second, we will apply two change-score multilevel regression models; one for the PTSD symptom severity outcome and one for the substance use outcome, with control variables (age, race, ethnicity, gender, relationship status, level of education, income level, employment status, health insurance status, provider and housing status), significant secondary outcome variables (quality of life, past barriers to substance use treatment, perception of recovery, self-stigma, substance craving, emergency department utilization and hospital treatment facility utilization) and predictor variables mentioned above. Examination of the multilevel regression model will allow for examination of client level deviation of the outcome variables by the time and predictor variables. *Post-hoc* analysis of the correlation matrix and pairwise t-tests of secondary outcomes and pre-post measurement will be examined to understand the impact of the markers in relation to the full scale of the data. Models will be used to assess for statistical robustness using the variance inflation factor for multicollinearity and appropriate error distribution tables. Latent-trait variables will be assessed for internal validity using exploratory factor analysis and reliability using Cronbach’s Alpha measure of internal consistency. While the primary outcome endpoint will be 120 days post-baseline, we will conduct secondary analyses to examine outcomes for participants using the last follow-up date post-baseline.

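### The CSQ-8 at baseline and at follow-up rates different services, so its paired difference is not a change in treatment satisfaction and its baseline score is not a treatment-satisfaction predictor

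*Protocol article*

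**What the plan says.** Table 1 (Outcomes) lists the domain Treatment Satisfaction, measured by the "Client Satisfaction Questionnaire (CSQ-8) (47", at "Baseline and every 60 days", with the variable type "Secondary Outcome and Predictor".

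The section on surveys of hospital staff and peer support workers (PSWs) explains why the CSQ-8 is in the battery: "to provide an opportunity for participants enrolled in the study to voice their opinions about the acceptability of the intervention".

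Under Effectiveness of the multi-level intervention, the plan says "we will test for significant pre-post differences in our secondary outcomes". It uses paired t-tests that run from the beginning to the end of the client's time in the program, and it reads the results as program impact on how clients perceive it. The CSQ-8 is not exempted. The same section names the predictors of change in both primary outcomes as "criminal justice involvement, motivation to change and client treatment satisfaction".

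On timing, Participant interviews and consent states: "Once an individual agrees to engage in treatment, the PSW provides details about the opportunity to participate". A release, contact by the research team, consent and the baseline interview follow. The Multi-level intervention section places Seeking Safety and pharmacotherapy after hospital discharge, by telehealth.

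**The concern.** A paired pre-post test assumes that the same quantity is measured twice. Most instruments in Table 1 meet this: craving, self-stigma or quality of life can be rated before and after treatment with the same meaning. Satisfaction with a treatment cannot be rated before the treatment has been received.

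If the stated test is run, it can return a significant rise or fall in satisfaction that only reflects a switch from rating the hospital encounter to rating the telehealth treatment. The plan would read that as program impact. In the primary models, a coefficient labelled treatment satisfaction could in fact describe how the participant felt about the hospital contact.

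**Working it through.** The point rests on measurement timing, and the plan gives no figure to reproduce. The check sets the sections side by side.

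**1. What a participant has received by baseline.** From Screening for SUD in the hospital, Communication post screening and Motivational interviewing: the TAPS screen (for some, a brief screen first), feedback of the result, motivational interviewing, a treatment menu and a discharge packet. From Participant interviews and consent: the cohort study is raised once the person has agreed to treatment, and the baseline interview comes after consent. From Multi-level intervention: Seeking Safety and pharmacotherapy start after discharge. So hospital and PSW contact is the only exposure established at baseline.

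**2. What is rated at follow-up.** For those who attended, Seeking Safety, pharmacotherapy or both. For those who agreed but never attended a session, still only the hospital contact and later attempts to engage them.

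**3. What the paired difference contains.** Among participants who attend at least one session by follow-up, let:

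- p = the share who had already had a session when the baseline interview took place (not given in the article, so anywhere from 0 to 1);
- H = the mean baseline rating of the hospital contact among those with no session yet;
- T0 = the mean early rating of treatment among those who had started;
- T1 = the mean follow-up rating of treatment, taken as equal in both groups for simplicity.

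Baseline mean = (1 − p)·H + p·T0. Follow-up mean = T1. Therefore:

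mean paired difference = p·(T1 − T0) + (1 − p)·(T1 − H)

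Only the first term is a change in treatment satisfaction. The second is a contrast between two services.

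- At p = 0, the order the article implies, the difference is T1 − H and holds no change in treatment satisfaction at all.
- At p = 1, the difference is T1 − T0, but the *pre* score was then taken after treatment began, so it is not a pre-treatment value.
- In between, it is a blend with unknown weights.

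No value of p yields a pre-to-post change in treatment satisfaction.

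**4. The predictor role.** The article does not say which visit supplies the value, so both cases apply. A baseline value is mainly H, a rating of the hospital contact. A follow-up value does rate the treatment, but it is taken after treatment starts and alongside the outcome. People who improve may report more satisfaction, so the direction of any association is open.

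**5. Extent.** Table 1 has ten secondary outcomes: criminal activity, motivation, satisfaction, quality of life, barriers, recovery, self-stigma, craving, emergency department use, and hospital or treatment facility use. The CSQ-8 is one of the ten and one of the three named predictors, which enter both primary models.

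**The case against.** Several points on the other side stand, and they limit what can be claimed.

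- **A reader might infer that the baseline CSQ-8 data are worthless.** The documents do not support that. Hospital screening is the first level of the intervention, and motivational interviewing runs through both levels. A baseline score can therefore rate a real study component; it just does not rate the treatment.
- **A reader might take it as fact that baseline precedes treatment.** The article never says so. It follows from the order of steps and from the plan's own pre and start labels. Step 3 shows that the conclusion does not depend on it.
- **A reader might infer that the participant-acceptability or feasibility answer rests on the pre-post comparison.** It does not. The staff-surveys section says only that the CSQ-8 lets participants give their opinion, and the Feasibility analysis names no CSQ-8 change. Interpretable follow-up scores will exist under the current schedule.
- **The paired test reaches the CSQ-8 by class, not by name.** The list of secondary outcomes that may enter the regression as covariates omits satisfaction, along with the two other named predictors. The first-step tests are still stated for the secondary outcomes without exception, and Table 1 makes the CSQ-8 one of them.
- **Post-treatment measurement of a predictor is not peculiar to the CSQ-8.** Motivation, craving, self-stigma and quality of life in the same models may share it. What is specific to the CSQ-8 is that its baseline value does not measure the named construct.
- **Which visit supplies the predictor can be left to an analysis plan.** Agreed, and that silence is not the point. The time point, role and test are fixed in the article, and together they produce a change score without a common referent.

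**Conclusion.** The point holds in limited form. As written, the plan tests a CSQ-8 change score whose two halves rate different services, or whose first half mixes treated and untreated people. That difference cannot be read as a change in treatment satisfaction. If the baseline score is the predictor, it is not satisfaction with this treatment either.

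The conclusion rests on two assumptions: that the phrase about secondary outcomes includes every variable Table 1 so labels, and that the baseline form has no separate, stated referent. The article gives none, and it ties the CSQ-8 to acceptability of the intervention.

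The effect is confined to one of ten secondary change tests and one of three named predictors. The primary outcome measures and the sample size are unaffected. It should be corrected before analysis because the correction is nearly free, but it does not threaten the study's main question.

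**What to change.** 1. Exclude the CSQ-8 from the pre-post paired t-tests.
2. Report the day-60 and day-120 CSQ-8 means with 95% confidence intervals as the level of acceptability, for all interviewed participants and also split by whether any treatment session was attended. Do not restrict the summary to attenders. That would remove people who agreed to treatment and never started, whose views matter given the engagement problems described in the Discussion.
3. Do not use the baseline CSQ-8 as the treatment-satisfaction predictor in the two primary models. If a follow-up score is related to outcome, label the association descriptive, because it is measured after treatment starts.
4. If baseline CSQ-8 data are kept, describe them only as a rating of the hospital and PSW contact.

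The cost is one secondary change test, one predictor and a few lines of analysis wording. The interview schedule need not change, and no follow-up data are discarded.
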